Though integrated emergency care systems are considered a solution for providing accessibility to emergency care in diverse geographical settings, evidence based information for planning and implementing a patient centric integrated emergency care system, particularly in low resource settings, is required. Therefore, in the initial phase of the study we plan to conduct:(i) a systematic literature review: to synthesise evidence for an integrated emergency care system, which has been adopted globally or within India to meet the needs of the population served. This will provide an overview of what has been tried to be integrated and its purpose; how this can be used to develop the model, processes, strategies and structure within the context of the needs of the population of selected districts. (ii) health system readiness: a. health facility and pre-hospital (ambulance and helpline centres) resource and infrastructure assessment in the study district and a defined area in adjoining districts; b. Mapping of emergency care system: geo spatial mapping of facilities; mapping of current emergency care pathways, care processes and referral pathways using observation checklists, direct observation, and interview with health care providers; c. competency assessment of care providers and 1^st^ responders to assess the knowledge and skills of healthcare providers; d. budgetary provisions abstracted from administrative data including public and private insurance systems and; e. indicators of the current state of emergency care, e.g., hospital emergency visits, types of emergencies, patient outcomes.(iii) A community-based household survey: to estimate the burden of EMDs in the community and assess the health care services sought after the event. The survey data will provide information on the proportion who sought care, pathway of care & referral pathway, delay in seeking care, the expenditure incurred during care provision for the emergency medical condition and utilisation of insurance services. A multistage sampling strategy will be adopted. The study population will be stratified into urban and rural areas. Villages will be the primary sampling unit (PSU) in rural areas. Villages with a population of less than 500 will be excluded from the sampling frame, and villages with a population of more than 5000 will be split into clusters to have an approximate population of around 2000 in each cluster. In an urban area, census enumeration blocks will be a PSU. Sample size is calculated to estimate the burden of emergency medical conditions. Considering the burden of emergency conditions as 141/10000 population (Table 2), assuming a confidence level of 95% and a relative precision of 25% and design effect of one (design effect is considered as one as due to rarity of outcome the events are less likely to be clustered), the required sample size is 4292. Considering a non-response rate of 20% the sample size comes out to be 5365 which is further rounded off to 6000. A total of 60 PSUs will be randomly selected (PSU stratification for urban and rural will be based on district’s urban:rural distribution) and 100 households will be randomly selected from each PSU. All the individuals in the selected household will be included for the purpose of data collection.

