
**Table 2 pone.0331290.t002:** Burden of emergency conditions.

Baseline coverage (%)	End line coverage (%)	Number required who had an emergency medical condition	Population to be surveyed
10	20	216	16241
	30	69	5188
	40	36	2707
20	30	311	23383
	40	89	6692
	50	43	3233
30	40	373	28045
	50	101	7594
	60	46	3759
40	50	405	30451
	60	104	7820
	70	46	3459
	80	25	1880

The qualitative component of the formative research will involve semi-structured interviews, focus groups, and surveys with key stakeholders, including administrators, policymakers, healthcare providers, first responders, paramedics, community groups, and patients. These interactions aim to gather diverse perspectives on state and district-level policymaking, program implementation, and financing options. Additionally, experiences and best practices from existing state-led programs like TAEI in Tamil Nadu and ambulance systems in Gujarat and STEMI and stroke models in Ludhiana will be explored [14–16]. Components of formative research, stakeholders, data collection techniques and sample size for each activity is provided in S1 Table.

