Evaluation will be done at baseline, concurrently during the implementation of the model and at the endline(S5 Table). Baseline, concurrent evaluations, and end-line survey data will be analysed to assess the feasibility, acceptability and the cost of the implementation of the model, and the effectiveness of the implemented model in terms of emergency care preparedness and coverage. Concurrent evaluation: Health facility assessment, qualitative interview with stakeholders, competency assessment of care providers will be done concurrently at an interval of three months. Post-care interviews (telephonically) of patients will be done to assess coverage and timeliness of care, expenditure, pathway of care, and delay in care. Endline evaluation: Endline survey will be conducted after the completion of the implementation phase. The sampling strategy and methodology of the endline survey will be similar to the baseline survey. Objective of the endline survey will be to estimate the increase in population coverage and health facility preparedness as compared to the baseline. The estimate of population coverage (i.e., reaching the appropriate health facility within a specified time frame as per the condition; this time frame will be decided during the formative research) obtained during the baseline survey will be used to calculate the sample size for the endline survey. Thus, the sample size for the endline survey will be calculated after the analysis of the results of the baseline survey. We are providing an illustration for sample size required for different scenarios of population coverage assuming a power of 80%, the confidence level of 95%, and a non-response rate of 20%. Thus, sample size included in baseline survey (at the district level) will be sufficient if there is at least 20% increase in population coverage from pre-intervention to post-intervention.

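### Table 2 gives cases needed in each of two equal rounds, but only the endline can still be sized; if the baseline is 6,000 persons, the 80% power fails for 10-point and most 20-point rises

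*Protocol article*

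**What the plan says.** **Baseline.** Under Formative research, the household survey is sized to estimate the burden of emergency conditions: 4,292, raised for 20% non-response to 5,365, and then "the sample size comes out to be 5365 which is further rounded off to 6000". The field plan in the same paragraph is 60 sampling units of 100 households, with every household member included. The Abstract gives 30,000 for five districts.

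**Endline.** The endline text stands under Secondary outcomes, in the evaluation section. It sets the purpose: "Objective of the endline survey will be to estimate the increase in population coverage and health facility preparedness as compared to the baseline". On timing it says: "Thus, the sample size for the endline survey will be calculated after the analysis of the results of the baseline survey", with the baseline coverage estimate as the input.

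**Table 2.** The table is offered as an illustration, "assuming a power of 80%, the confidence level of 95%, and a non-response rate of 20" per cent. Its case column is headed "Number required who had an emergency medical condition" and does not say whether the count is per round or in total. The paragraph then concludes that the district-level baseline size suffices if coverage rises by at least 20%.

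**The concern.** A comparison of two survey rounds has two sources of sampling error. When the endline size is chosen, the baseline part is already set by the number of baseline patients found. A formula that assumes two rounds of the same size answers a different question. It gives the stated power only if the baseline happened to yield at least the tabulated number of cases.

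Coverage is the primary outcome, and Table 2 is the only sizing method shown for it. If the table were used to choose the endline alone, a district looking for a small rise could field a very large survey (30,451 people in the 40 to 50% row) and still have well under 80% power. A null result could then be misread as a failure of the model.

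**Working it through.** **1. Reproducing Table 2.** Inputs from the endline text: power 80% and confidence 95%, taken as two-sided. With q = 1 − p and d = p2 − p1:

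- n = (1.96 + 0.84)² (p1q1 + p2q2) / d²
- with continuity correction: n_cc = (n/4) [1 + √(1 + 4/(n d))]²

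For 40 to 50%: n = 7.849 × (0.24 + 0.25) / 0.01 = 384.6, and n_cc = 404.3, tabulated as 405. Likewise 10 to 20% gives 215.8 (216), 20 to 30% gives 310.1 (311), 30 to 40% gives 372.9 (373), 30 to 50% gives 100.0 (101) and 40 to 60% gives 103.9 (104). All 13 counts agree to within one case. A one-sample formula gives 86, 137, 172 and 191 for the 10-point rows, so it is ruled out. The counts are therefore per round, with both rounds equal.

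**2. Baseline cases.** The burden is 1.41% in the text and 1.33% as implied by Table 2 (for example 216/16,241).

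- *6,000 persons:* 6,000 × 0.0133 to 0.0141 = 80 to 85; after 20% non-response, 4,800 × the same = 64 to 68. Range 64 to 85.
- *6,000 households:* household size is not in the document. Assuming 4.5 members, 27,000 × 0.8 × 0.0141 = 305. At 1.33%, with and without non-response, this is 287 to 359.

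**3. Power with the baseline held fixed.**

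- SE² = p1q1/n1 + p2q2/n2
- c = ½(1/n1 + 1/n2), or 0 without the correction
- power = Φ[(d − c)/SE − 1.96]

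The pooled-variance version of the test was run as well.

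Example, 40 to 50%, n1 = 80, n2 = 405: SE = √(0.24/80 + 0.25/405) = √(0.00300 + 0.00062) = 0.0601. Power is Φ(1.663 − 1.96) = 38% without the correction and 34% with it. With an unlimited endline only 0.24/80 remains: Φ(0.1/0.0548 − 1.96) = 45%.

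Ranges below cover pooled and unpooled variance, with and without the correction. The ceiling is the power with an unlimited endline.

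| Rise | Table 2 cases | Power, n1 = 64–85 | Ceiling, n1 = 64–85 | Power, n1 = 305 |
|---|---|---|---|---|
| 10→20 | 216 | 36–65% | 69–87% | 85–89% |
| 20→30 | 311 | 29–51% | 45–64% | 79–82% |
| 30→40 | 373 | 27–43% | 36–52% | 75–78% |
| 40→50 | 405 | 27–40% | 33–47% | 73–76% |
| 10→30 | 69 | 76–88% | over 99% | 91–97% |
| 20→40 | 89 | 70–84% | 97% or more | 92–96% |
| 30→50 | 101 | 67–81% | 92–98% | 93–95% |
| 40→60 | 104 | 66–80% | 88–96% | 93–95% |
| Five rows, 30 points or more | 25–46 | 84–99% | over 99% | 93% or more |

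**4. When no endline is large enough.** 80% power is unattainable if n1 ≤ p1q1 × 7.849/d². For a 10-point rise from 10, 20, 30 and 40% that is about 71, 126, 165 and 189 baseline cases. With 64 to 85 cases the last three are out of reach. At 80 cases and without the correction, their ceilings are 61%, 50% and 45%. The 10 to 20% row is borderline; with 85 cases and Table 2's own corrected test it needs about 2,466 endline cases.

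**5. Endline cases needed with n1 fixed.** On the persons reading and with Table 2's test, rises of 20 points from 20, 30 and 40% need about 91–120, 118–193 and 134–277 cases, against 89, 101 and 104 tabulated. With 305 baseline cases, 40 to 60% needs only about 56 to 63 against 104, whereas 40 to 50% needs about 514 to 589 against 405.

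**The case against.** A reader might infer that the tabulated endline sizes miss 80% power in general, and that no larger endline can help. The document does not support that. On the persons reading, six of the 13 rows are on target or above it, and 20 to 40% is marginal. On the household reading, a finite endline reaches 80% in every row.

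Four further points deserve weight.

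- **Table 2 is an illustration.** The formula for the later calculation is not given and may properly hold the baseline fixed. That stands: the protocol has not adopted a wrong endline size. But the table is the only method shown for the primary outcome, it states 80% power, and a sufficiency conclusion is drawn from it.
- **The protocol limits itself to rises of at least 20%.** It does not claim that 6,000 is enough for 10-point rises. However, three of its own 20-point rows call for 6,692, 7,594 and 7,820, and the table still lists larger surveys for smaller rises.
- **The aim is 80% coverage.** From any tabulated baseline that is a rise of at least 40 points, and the 40 to 80% row has 92 to 99% power. Nothing in the document says that a district plans for a 10-point rise. This limits the practical harm.
- **A larger endline is not pure waste.** It sharpens the endline estimate against the 80% target. Pooling five districts (30,000 × 0.0133, about 400 cases) would also bring the tabulated sizes to about 80% or more, but the sufficiency statement is made at district level.

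**Conclusion.** The point holds in a limited form. Table 2 is computed correctly for two equal rounds, but the plan sizes one round against a baseline already fixed for another purpose. The stated 80% power therefore fails wherever the baseline yields materially fewer cases than the table lists.

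On the persons reading, which the 4,292 to 5,365 to 6,000 arithmetic implies, the shortfall is large for the four 10-point rows and modest for 20-point rises from 20, 30 and 40%. On the household reading it is confined to 30 to 40% and 40 to 50%, and the larger-rise rows ask for more cases than needed. Across 287 to 359 baseline cases, those two short rows run from about 72 to 81%.

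The size of the problem thus depends on a unit that the document leaves unresolved and on an assumed household size. The need to hold the baseline fixed does not depend on either.

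**What to change.** - State whether 6,000 per district is persons or households.
- Label the Table 2 case column *per round, both rounds of this size*.
- Calculate the endline with n1 fixed at the number of baseline cases actually found in the district: n2 = p2q2 / [(d/(1.96 + 0.84))² − p1q1/n1], with the continuity correction added if it is kept.
- Where the bracket is zero or negative, so that 80% power is unattainable, report the smallest detectable rise or the attained power instead of enlarging the endline.
- Limit the 80% power statement, and the sufficiency statement for rises of at least 20%, to the scenarios that deliver them.

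The cost is one formula, one label and a few sentences. The baseline survey need not change, and under the plan the endline size is set only after the baseline is analysed. The only downside is that the stated 80% power is withdrawn for small rises.

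### Table 2's survey populations do not follow from the stated burden (141 per 10,000) and 20% non-response; they are about 15% too small, and one row has a further slip

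*Protocol article*

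**What the plan says.** The baseline calculation is in the Formative research section. Its burden is introduced with "Considering the burden of emergency conditions as 141/10000 population (Table 2"), and the remaining inputs follow in the same sentence: "assuming a confidence level of 95% and a relative precision of 25% and design effect of one". This gives 4,292. Non-response is then added: "Considering a non-response rate of 20% the sample size comes out to be 5365 which is further rounded off to 6000". The sample is 60 primary sampling units with 100 households each, and everyone in a chosen household is included.

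Table 2 is captioned as a table of burden but shows none. It lists pairs of baseline and endline coverage with two result columns, "Number required who had an emergency medical condition" and, beside it, "Population to be surveyed".

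The inputs for these scenarios come later, in the endline paragraph under Secondary outcomes: "assuming a power of 80%, the confidence level of 95%, and a non-response rate of 20" per cent. That paragraph calls the scenarios an illustration and leaves the endline size until the baseline results are analysed. It then concludes that the "sample size included in baseline survey (at the district level) will be sufficient if there is at least 20% increase in population coverage".

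**The concern.** The inputs and the results are both printed, so the table can be checked, and the population column does not come out of the stated inputs. Coverage is the primary outcome, and this column is the only support for saying that the baseline size is large enough to detect a 20-point rise. If the column is too small, that statement rests on requirements that are too low. A team that copied the method when sizing the endline would also plan for too few emergency cases.

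**Working it through.** **Inputs.** Power 80%, 95% confidence and 20% non-response (endline paragraph). Burden 0.0141 and design effect 1 (Formative research). Cases and populations from Table 2.

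**Step 1: the protocol's baseline figure.** 1.96² × (1 − 0.0141) / (0.0141 × 0.25²) = 4,298, against 4,292 printed; a burden of 0.01412 gives 4,292. Then 4,292 / 0.8 = 5,365, as printed. So the baseline uses 141 per 10,000, and non-response is handled by dividing by 0.8. A burden of 0.0133 would have given 4,560.

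**Step 2: case counts.** With a two-sided 5% level, 80% power and unpooled variance:

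n = [p1(1 − p1) + p2(1 − p2)] × (1.960 + 0.842)² / d², where d is the difference in coverage.

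The continuity correction is n′ = (n/4) × [1 + √(1 + 4/(n·d))]². For 10% to 20%, n = 196.2 and n′ = 215.8, which rounds up to 216. Rounded up, this reproduces all 13 counts with no non-response added.

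**Step 3: populations** (nearest whole person; rounding up adds at most one).

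| Coverage, % | Cases printed | n′ | Population printed | Cases / 0.0133 | Cases / 0.01128 |
|---|---|---|---|---|---|
| 10 to 20 | 216 | 215.8 | 16,241 | 16,241 | 19,149 |
| 10 to 30 | 69 | 68.5 | 5,188 | 5,188 | 6,117 |
| 10 to 40 | 36 | 35.1 | 2,707 | 2,707 | 3,191 |
| 20 to 30 | 311 | 310.1 | 23,383 | 23,383 | 27,571 |
| 20 to 40 | 89 | 88.2 | 6,692 | 6,692 | 7,890 |
| 20 to 50 | 43 | 42.2 | 3,233 | 3,233 | 3,812 |
| 30 to 40 | 373 | 372.9 | 28,045 | 28,045 | 33,067 |
| 30 to 50 | 101 | 100.0 | 7,594 | 7,594 | 8,954 |
| 30 to 60 | 46 | 45.7 | **3,759** | 3,459 | 4,078 |
| 40 to 50 | 405 | 404.3 | 30,451 | 30,451 | 35,904 |
| 40 to 60 | 104 | 103.9 | 7,820 | 7,820 | 9,220 |
| 40 to 70 | 46 | 45.7 | 3,459 | 3,459 | 4,078 |
| 40 to 80 | 25 | 24.4 | 1,880 | 1,880 | 2,216 |

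The divisor 0.0133 fits every row but 30 to 60. There the same 46 cases give 3,459, as printed in the 40 to 70 row.

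**Step 4: size of the gap.** 1 − 0.01128/0.0133 = 15.2%, and 0.0133/0.01128 = 1.179. In the 30 to 60 row, 3,759 is 7.8% below 4,078. Applying non-response as × 1.2 does not rescue the column: 216 / 0.0141 × 1.2 = 18,383, not 16,241.

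**Step 5: the sufficiency statement.** I read the 20% increase as percentage points, as the table is laid out.

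- If 6,000 is individuals: as printed, 5,188 is met, and 6,692, 7,594 and 7,820 are not. Recomputed, 6,117, 7,890, 8,954 and 9,220 are all above 6,000, the first by 117 (2%).
- If 6,000 is households: the largest recomputed need, 9,220, is met once households average 9,220 / 6,000 = 1.54 members. The document gives no household size.

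**The case against.** **The table is an illustration.** The endline size is to be calculated from baseline results, so Table 2 fixes no survey size. This stands. A reader might infer that the endline survey will be about 15% too small, but the document does not say that it will be sized from this column. It equally does not say that the later calculation will ignore the number of cases already fixed at baseline, so no criticism of equal group sizes is made here.

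**The cause is not identified.** A reader might infer that the authors used 133 per 10,000 and left out non-response. The column shows only the product, burden × response = 0.0133. That fits 133 with no non-response, 141 with 5.7% non-response (1 − 0.0133/0.0141), or about 166 with the full 20% (0.0133/0.8 = 0.0166). Neither 133 nor 166 is stated anywhere, and the endline paragraph does not repeat 141. This stands as to cause. It does not remove the mismatch, since 141 is the only burden given and it is tied to Table 2.

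**Non-response might already be in the case counts.** A one-sided 5% calculation divided by 0.8 comes close, but gives 217.5 against 216 and 403.3 against 405. The two-sided calculation without inflation matches every row. Even under the one-sided reading, 141 would give 216 / 0.0141 = 15,319, not 16,241.

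**The 6,000 may be households.** Sixty units of 100 households is 6,000 households, yet 6,000 was derived from a per-person burden. Both readings have support, so a flat claim that the baseline is too small is not supported.

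**Conclusion.** The point holds as an error in printed figures. Table 2's populations cannot be obtained from 141 per 10,000 and 20% non-response. On those inputs, 12 of 13 are 15.2% too small, and the 30 to 60 entry is a separate slip. This rests on taking the case counts as free of non-response, which their exact match to the two-sided formula supports, and on carrying 141 over from the baseline section.

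The sufficiency statement is unsafe as written. With 6,000 individuals it contradicts the table even before any recomputation; with 6,000 households it may be true. The document does not settle which is meant. The effect is confined to the printed sizes and that statement, because the endline size is still open.

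**What to change.** - Recompute the population column as cases / (0.0141 × 0.8). Otherwise, state and justify the burden and non-response actually used, and use the same burden for the baseline. If 133 is kept with 20% non-response, the column rises by 25% (216 / (0.0133 × 0.8) = 20,301) and the baseline becomes 4,560 / 0.8 = 5,700, still under 6,000.
- Correct the 30 to 60 entry: about 4,078 on the stated inputs, or 3,459 on the table's present divisor.
- Correct the caption of Table 2 and the citation of it for the burden, and give the source of 141 per 10,000.
- State whether 6,000 is persons or households per district, and restate the sufficiency sentence to match, in percentage points.

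The cost is one recalculated column and a few sentences. On the stated inputs the illustrated sizes become about 18% larger. No fixed endline size changes.

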**Methodology:**

The proposed implementation research is designed as a mixed methods study to be conducted over a 3-year period in selected districts of the states of Punjab, Gujarat, Madhya Pradesh, Odisha and Puducherry. The public/private medical college hospital/ tertiary care hospital in the district will serve as a hub and primary health care services as spokes. The health facilities will be graded according to the availability of resources for their readiness and preparedness to provide care for handling a particular emergency condition. The steps to build and implement the model are: 1. a gap analysis related to emergency care at both pre-hospital and health facility level; 2. a community-based survey in a sample of 30,000 in 5 districts for EMD burden estimates and health-seeking behaviour at baseline and endline; 3. use a consolidated framework for implementation research to develop, optimise and implement hub and spoke model through three cycles of iterative processes; and; 4.evaluation for feasibility, acceptability, cost, effectiveness and coverage.

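### The sufficiency sentence for a 20-point rise in coverage contradicts Table 2 if the district sample is 6,000 persons and holds if it is 6,000 households; the unit is not settled, and Table 2's population column departs from its stated inputs

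*Protocol article*

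**What the plan says.** **District size.** Under Formative research, the household survey is sized to estimate a burden of 141 per 10,000 population with 25% relative precision, 95% confidence and a design effect of one. This gives 4,292, and then "Considering a non-response rate of 20% the sample size comes out to be 5365 which is further rounded off to 6000".

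**Sampling.** The same paragraph selects 60 primary sampling units per district. It adds that "100 households will be randomly selected from each PSU" and that "All the individuals in the selected household will be included for the purpose of data collection". The Abstract describes "a community-based survey in a sample of 30,000 in 5 districts" without naming a unit.

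**Power for coverage, the primary outcome.** The endline paragraph under Secondary outcomes leaves the endline size until baseline results are known. It offers Table 2 as an illustration, "assuming a power of 80%, the confidence level of 95%, and a non-response rate of 20" per cent. It then concludes that the "sample size included in baseline survey (at the district level) will be sufficient if there is at least 20% increase in population coverage".

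**Table 2, 20-point rows:**

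| Baseline to endline | Cases needed | Population to survey |
|---|---|---|
| 10% to 30% | 69 | 5,188 |
| 20% to 40% | 89 | 6,692 |
| 30% to 50% | 101 | 7,594 |
| 40% to 60% | 104 | 7,820 |

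**The concern.** The sufficiency sentence is worded as a consequence of Table 2. Three of the four 20-point rows nevertheless exceed 6,000, the only district figure the document derives. The calculation behind 6,000 counts persons, while the sampling text makes it a count of households. The sentence is false on one reading and true on the other, and the article gives no household size with which to connect them.

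This is the only power statement for the primary outcome. A district team could rely on it when deciding whether repeating the baseline size at endline is enough. If the 6,000 were implemented as persons, that decision would rest on a wrong figure.

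**Working it through.** **1. The precision calculation.** With p = 0.0141 and relative precision 0.25:

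1.96² × (1 − p) / (0.25² × p) = 3.8416 × 0.9859 / 0.00088125 ≈ 4,298 (stated: 4,292).

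4,292 / 0.8 = 5,365, rounded up to 6,000. The input is a rate per person, so the result is a number of persons.

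**2. Table 2's case counts.** With d = p2 − p1, two-sided 5% and 80% power:

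n = (1.96 + 0.8416)² × [p1(1 − p1) + p2(1 − p2)] / d² + 2/d

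This reproduces all 13 case counts to within 1. For 20% to 40%: 7.849 × 0.40 / 0.04 + 10 = 88.5 (printed: 89). The formula is inferred from this match; the article does not state it.

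**3. Table 2's population column.** Cases / 0.0133 reproduces 12 of 13 rows: 69 gives 5,188, 89 gives 6,692, 101 gives 7,594 and 104 gives 7,820. The exception is 30% to 60%, where 46 / 0.0133 = 3,459 but 3,759 is printed. The 40% to 70% row has the same 46 cases and prints 3,459. The column therefore uses 133 per 10,000, not 141, and includes no inflation for non-response.

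**4. If 6,000 means persons.** The shortfalls against Table 2 are 692, 1,594 and 1,820 persons. Expected cases per round are 6,000 × 0.0133 = 79.8, and 79.8 × 0.8 = 63.8 after non-response. Inverting the formula in step 2:

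power = Φ( √[(n − 2/d) × d² / (p1q1 + p2q2)] − 1.96 ), where q = 1 − p.

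For 20% to 40% with 79.8 cases: √(69.8 × 0.04 / 0.40) − 1.96 = 0.68, so power is 75%.

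| Rise | 79.8 cases | 63.8 cases | 79.8 cases, pooled test without continuity term |
|---|---|---|---|
| 10% to 30% | 86% | 76% | 89% |
| 20% to 40% | 75% | 64% | 79% |
| 30% to 50% | 69% | 58% | 74% |
| 40% to 60% | 67% | 56% | 72% |

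**5. Table 2 with its stated inputs.** Persons = cases / (0.0141 × 0.8):

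- 69 / 0.01128 ≈ 6,117
- 89 / 0.01128 ≈ 7,890
- 101 / 0.01128 ≈ 8,954
- 104 / 0.01128 ≈ 9,220

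On the persons reading, even the 10% to 30% row now exceeds 6,000. The available cases are 6,000 × 0.0141 × 0.8 = 67.7 against 69 needed, and power is about 79%.

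**6. If 6,000 means households with all members surveyed.** The largest 20-point row needs 7,820 / 6,000 = 1.30 persons per household. With 20% non-response it needs 7,820 / 0.8 / 6,000 = 1.63 at 133 per 10,000, or 9,220 / 6,000 = 1.54 at 141 per 10,000. Household size is not given. If 3 to 5 members are assumed (18,000 to 30,000 persons), power is at least 97% in every 20-point row after 20% non-response.

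**The case against.** The strongest reply is that the sampling text settles the matter. It draws 60 × 100 households and includes everyone in them, and Table 2 counts persons. Any plausible household size then covers all four 20-point rows, and the sentence is correct. It even fits as a threshold: at an assumed 4 to 5 members (24,000 to 30,000 persons) not every 10-point row is met, since 40% to 50% needs 30,451. Of the steps tabulated, 20 points is then the smallest that holds at every baseline. This stands as a reading of the sampling text. It does not explain why 6,000 is derived as persons, and no household size is given to link the two.

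The second reply is that the endline size is not fixed at 6,000. That also stands. The article sets it after baseline, so the power figures in step 4 describe an equal endline only. On the persons reading, an endline about 1.6 times the baseline would bring the three deficient rows to 81–87% (pooled formula, 79.8 baseline cases, before non-response). The sentence nonetheless asserts sufficiency in advance.

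The third reply is that the power figures depend on the formula. Without the continuity term the 20% to 40% row is 79%, almost on target. The other two rows stay below 80% with either formula.

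**Conclusion.** The sufficiency sentence does not follow from Table 2 if the district sample is 6,000 persons. Three of four rows then fall short, with power of about 67–75% before non-response and 56–64% after it. These figures assume an equal endline, Table 2's inferred formula and yield, and the article's design effect of one. If the sample is 6,000 households with all members surveyed, the sentence is true. Separately, and on either reading, Table 2's population column does not use the burden and non-response that the text states.

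A reader might infer three stronger conclusions that the documents do not support:

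- **That the study will not deliver 80% power.** This holds only on the persons reading, and the sampling text points to households.
- **That districts with 20–40% baseline coverage will have an underpowered endline.** The endline size is calculated later from observed baseline coverage.
- **That on the household reading the sentence is wrong the other way.** A sample able to detect smaller rises is still sufficient for 20 points. The sentence would merely understate what some districts can detect.

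Reading 20% as a relative increase would make the sentence fail more widely, but Table 2's layout supports percentage points.

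**What to change.** 1. State whether 6,000 per district and 30,000 overall are persons or households and, if households, the assumed mean size.
2. Recompute Table 2's population column with 141 per 10,000 and 20% non-response, or state the values actually used. Check the 30% to 60% entry (3,759 printed, 3,459 expected from the table's own yield).
3. Replace the sufficiency sentence with the detectable difference, in percentage points and by baseline coverage, for the resulting number of persons.

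For orientation, solving the step 2 formula for d at 141 per 10,000, 20% non-response, equal rounds and 80% power gives:

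| District sample | Cases per round | Baseline 10% | 20% | 30% | 40% |
|---|---|---|---|---|---|
| 6,000 persons | 67.7 | 20.2 | 23.2 | 24.6 | 24.8 |
| 6,000 households, 3 members (assumed) | 203 | 10.4 | 12.6 | 13.8 | 14.2 |
| 6,000 households, 5 members (assumed) | 338 | 7.7 | 9.5 | 10.5 | 11.0 |

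It would not be enough to say that 6,000 persons suffice for a 20-point rise from a 10% baseline, because after non-response that row also falls just short of 80%.

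The cost is a recalculated column and a few sentences. It adds no participants. If persons are meant, the stated detectable difference becomes less favourable; if households are meant, it becomes more favourable.
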